### Criteria for discontinuing or modifying allocated interventions {11b}

Participants may discontinue or modify their participation if they experience major barriers to continuing (e.g., progression of disease, inability to complete follow-up).

### Strategies to improve adherence to interventions {11c}

To maximize clinician fidelity to the intended use of the tool we will train each participating clinician, periodically check video recordings for fidelity, and provide feedback and retraining as necessary.

### Interventions: concomitant care {11d}

All other care and interventions, as determined by the treating clinician, will be permitted during the trial.

### Provisions for post-trial care {30}

No provisions for ancillary or post-trial care will be provided, as the study does not involve any physical interventions.

### Outcomes {12}

Patient outcomes, Primary Endpoints:

To assess the primary endpoint of SDM process quality, two measures will be collected.

#### SDMQ-9:

a self-reported 9 item questionnaire that assesses the effectiveness of the intervention on promoting SDM. Each item has a six-point Likert-type scale that ranges from 0 (Completely disagree) to 5 (Completely agree). The overall score is the sum of the 9 items, where lower values indicate less perceived SDM, and higher scores indicate more perceived SDM (14).

#### OPTION12:

an observer scale applied to recorded encounters which assesses the degree of effort the clinician made to involve patients in SDM. The scale consists of 12 items scored from 0, no effort to 4, exemplary effort. The 12 items are summed and converted to a 100-point scale. Initially, a sample of 20% of the recordings will be assessed by two or more reviewers. Agreement will be assessed by Lin’s concordance index, where any value over 0.8 will be considered concordant. Once the agreement is reached, other videos will be reviewed. If concordance does not occur within the first 20% encounters, the two reviewers will assess cases of difference and review an additional 10 cases to test for agreement. Recordings scored by both reviewers will be averaged (15).

#### Patient Outcomes:

Secondary endpoints

#### Knowledge transfer:

estimated by asking 6 investigator-developed questions to patients about treatment options to prevent recurrence of lung cancer. The 6 questions use a response format of “True / False / Do not know.” Correct responses will be summed up and divided by the total number of questions asked. If a patient answers at least 1 knowledge question then they will be assessed for this outcome, where all missing responses will be coded as incorrect.

#### Patient Satisfaction with clinical encounter:

assessed with 1 question on a 7-point Likert scale. Patients will be asked whether they would recommend the approach used to others facing similar discussions.

#### Decisional Conflict Scale (DCS):

A 16-item scale assessing respondent uncertainty about a course of action. Each of the 16 DCS items is scored on a 0-4 Likert-type scale; the items are summed, divided by 16 and then multiplied by 25. The scale is from 0-100 where higher scores are reflective of uncertainty about the choice. There are 5 DCS subscales, where a DCS subscale consists of 3 questions (1 subscale of 4). If 2 of 3 (or 3 of the 4) questions within a subscale have responses, then the patient would be considered as a responder, and a score could be calculated. If more than one response per subscale is missing, then that specific subscale is not calculated for the patient. An overall DCS score can be calculated if no more than 5 responses are missing if each missing response falls into a different subscale. The entire scale will be administered 2 weeks post-encounter of interest and the subscales of informed, and uncertainty will be administered post encounter (16).

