#### Objective 2:

To estimate the extent to which NSCLC choice reduces decisional conflict compared to usual care. **Hypothesis:** Using NSCLC Choice reduces decisional conflict.

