## Statistical Methods

### Statistical methods for primary and secondary outcomes {20a} and {20c}

The study will be analyzed according to the *intention to treat principle (ITT)*, including all patients enrolled in the study and analyzed in the arm to which they were assigned, regardless of which intervention they received. Descriptive statistics will be conducted with means and standard deviations for continuous variables and counts and frequencies for categorical variables. We will use cluster (cluster at clinician level) adjusted t-test and chi-square test for comparisons between interventions and hierarchical generalized linear models (HGLMs) with random main effects specified at the clinician level when adjusting by more than arm. If clustering is not present, then the results will reduce to a model that assumes independence and reflects findings appropriately. Missing data will not be imputed for the analysis. Rates of missing data will be reported in the findings.

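### The only stated formula for the Decisional Conflict total divides by 16, yet totals are allowed with up to 5 items missing; followed as written, each skipped item scores as no conflict

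*Protocol article*

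**What the plan says.** Protocol article, Outcomes {12}, Decisional Conflict Scale (DCS):

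- Items and range: "Each of the 16 DCS items is scored on a 0-4 Likert-type scale".
- Total: "the items are summed, divided by 16 and then multiplied by 25".
- Direction: "The scale is from 0-100 where higher scores are reflective of uncertainty about the choice". An item scored 0 is therefore the least-conflict answer.
- Structure: five subscales, four with 3 items and one with 4.
- Incomplete forms: "An overall DCS score can be calculated if no more than 5 responses are missing if each missing response falls into a different subscale". A subscale can be scored with 2 of 3 or 3 of 4 answers. No formula is given for a subscale score, complete or not.

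Statistical methods {20a} and {20c}: "Missing data will not be imputed for the analysis".

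Objective 2 is "To estimate the extent to which NSCLC choice reduces decisional conflict compared to usual care". The DCS is the measure given for it and is listed among the secondary endpoints.

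**The concern.** The scoring formula and the missing-item rule do not fit together. The formula suits a complete form. The rule then admits forms with 11 to 15 answers without saying how the sum is to be scaled. A programmer working from this text has one divisor, 16, and an instruction not to impute. Using both gives every skipped item the most favourable value on the scale.

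At stake is the comparison of decisional conflict between arms. If patients in one arm skip more items, that arm looks less conflicted for a reason unrelated to the tool. If skipping is equal, both means fall by the same proportion and a true difference shrinks slightly. Skipped items are plausible, because the full scale is self-completed two weeks later by mail, email or portal message.

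It is also better settled now than at analysis. The analyst is not blind to arm (Who will be blinded {17a}), and the statistical team can access the data at any time (Data management {19}). A divisor left open could be chosen with results by arm in view.

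**Working it through.** **Inputs, all from the DCS section:** 16 items scored 0 to 4; total = sum / 16 x 25; at most one missing item in each of 5 subscales.

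**Step 1: reproduce the stated range.** Items: 4 x 3 + 4 = 16. Maximum: (16 x 4) / 16 x 25 = 100. Minimum: 0. The stated 0 to 100 range is correct for a complete form. Maximum missing: 5 x 1 = 5.

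**Step 2: compare the two scores for a form with m missing items.**

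- As written: sum of answered / 16 x 25.
- Prorated: sum of answered / (16 - m) x 25.
- Ratio: (16 - m) / 16, so the relative shortfall is m / 16.

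The last three columns show what a prorated score of 25, 40 or 50 becomes. These scores are illustrative; the protocol gives no expected DCS value.

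| m | Ratio | Shortfall | 25 becomes | 40 becomes | 50 becomes |
|---|---|---|---|---|---|
| 1 | 0.9375 | 6.25% | 23.4 | 37.5 | 46.9 |
| 2 | 0.8750 | 12.5% | 21.9 | 35.0 | 43.8 |
| 3 | 0.8125 | 18.75% | 20.3 | 32.5 | 40.6 |
| 4 | 0.7500 | 25% | 18.8 | 30.0 | 37.5 |
| 5 | 0.6875 | 31.25% | 17.2 | 27.5 | 34.4 |

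**Step 3: what 31.25% measures.** It is the largest shortfall against the prorated score. Against the total the patient would have had with every item answered, the shortfall depends on the unseen answers. With five skipped:

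- It is 0% if all five would have been 0.
- If all five would have been 4 and the other eleven are 1, the complete score is (20 + 11) / 16 x 25 = 48.4 and the scored value is 11 / 16 x 25 = 17.2, a 65% drop.
- If all five would have been 4 and the rest are 0, 31.25 becomes 0, a 100% drop.

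The absolute loss cannot exceed 5 x 4 / 16 x 25 = 31.25 points.

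**Step 4: effect on arm means.** The protocol gives no item-level missing rate, so this step rests on assumptions. Suppose an extra fraction p of patients in one arm skip k items, unrelated to their score. That arm's mean shifts down by mean x p x k / 16.

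- Mean 40, p = 10%, k = 1: 40 x 0.10 x 1/16 = 0.25 points.
- Mean 40, p = 30%, k = 2: 40 x 0.30 x 2/16 = 1.5 points.
- Lowest case with means of 25 to 50: 25 x 0.10 x 1/16 = 0.16 points. Highest: 50 x 0.30 x 2/16 = 1.9 points.

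With equal skipping in both arms, both means are multiplied by 1 - p x k / 16. This is 0.994 for the first pair of p and k and 0.9625 for the second. An assumed true difference of 10 points becomes 9.9 or 9.6.

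**Step 5: subscales.** If a fixed divisor were carried over to the subscales, one missing answer would cost 1/3 = 33% of a 3-item score or 1/4 = 25% of the 4-item score, against prorating. The protocol states no subscale divisor, so this only shows why the rule should cover them.

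**The case against.** The strongest reply is that the protocol never commits to the faulty score. The formula is introduced for the 16-item scale and can be read as describing a complete form. The missing-item rule comes later and says only when a total may be calculated. Three features favour averaging the answered items:

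- For the knowledge score, where a blank is meant to count as zero, the protocol says so: "all missing responses will be coded as incorrect". The DCS section has no such sentence.
- Scoring a blank as 0 amounts to imputing the best answer, which sits badly with the no-imputation statement.
- A limit of one missing item per subscale is the kind of condition that accompanies averaging.

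The article is also condensed, and the instrument's scoring instructions or an analysis plan may settle the divisor.

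Much of this stands. A reader might infer that the trial will always divide by 16; the text does not say so. A reader might also infer that the DCS result is biased by 31%. That figure is one patient's worst case, with an item skipped in all five subscales, and only relative to prorating. Nor do the documents show that skipping would be commoner with NSCLC Choice, so a bias in the tool's favour is not supported.

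What does not stand is that this is merely detail left to another document. The article fixes the item range, divisor, multiplier, number of tolerated blanks and their spread across subscales. As fixed, the parts yield a biased score if followed literally, and the no-imputation sentence could be read as barring the remedy.

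**Conclusion.** The point holds as a scoring rule that is badly fixed. As written, each skipped item lowers a patient's DCS total by 6.25%, up to 31.25% at five, relative to the mean of the answered items. This rests on reading the single stated divisor as applying to every form that is scored. The protocol neither confirms nor excludes that reading.

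The effect on the arm comparison is unknown in size and direction. Under the assumptions tried above it is about 0.2 to 1.9 points on a 100-point scale, so probably modest. Severity is moderate to low: the DCS is the measure for Objective 2, but the primary endpoint is SDM quality by SDMQ-9 and OPTION12, and the sample size rests on SDMQ-9. Nothing here threatens the primary conclusion.

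**What to change.** Replace the scoring sentence with: total DCS = (sum of answered items / number of answered items) x 25, calculated only when no subscale has more than one missing item. Score each subscale in the same way, dividing by the number answered. Add to the statistical methods that averaging answered items within a scale is part of scoring and is not imputation. Settle this before any results by arm are examined.

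The cost is a sentence or two of text. Data collection does not change, and totals for complete forms are identical under both formulas.

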#### Decision made on treatment:

derived from the recorded encounter. Decisions about whether and which therapy to follow may not be made within the encounter as the patient may wish to take some time to decide or may be contingent on test results not yet in hand (e.g. tumor mutation). In these cases, or if the final decision is not clear in the video recording, we will extract it from clinical documentation in the electronic health record (EHR).

### Clinician Outcomes

#### Satisfaction with the encounter:

assessed with 2 questions immediately after the patient encounters. A 5-point Likert-type scale will assess satisfaction with discussion about NSCLC choice. The clinician will also be asked whether they would recommend the approach used to other clinicians using a 7-point Likert-type scale (17).

### Participant timeline {13}

Patient’s participation in the study involves completing two questionnaires by each participant: one at baseline after the encounter of interest is complete, one at 2 weeks post enrollment, and EHR is reviewed at 6 weeks post enrollment (Figure 1). The initial questionnaires will either be provided in person or sent via email, based on the participant’s preference. Subsequent surveys will be automatically sent to the participant's email. The estimated time to complete each questionnaire is approximately 10 minutes.

### Sample size estimation {14}

The targeted sample size is 100 patients. SDMQ-9 has an estimated mean value of 70 at baseline, with a standard deviation of 20. Assuming an average cluster size of 5 patients per clinician and 20 clinicians, along with an intra cluster correlation coefficient (ICC) of 0.01, we would achieve 82% power to detect a 12-point increase in the intervention group (N=50 per group), using a two-sided test with an alpha of 0.05. If 10 clinicians are recruited, with an average cluster size of 10 patients per clinician, we would have 80% power.

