### Trial Design {8}

We will conduct a patient-level randomized controlled trial. Participants will be randomly assigned in a 1:1 ratio to either NSCLC Choice or usual care. Figure 1 graphically illustrates the overall design of the study. All study procedures will be approved by an institutional review board (IRB # 23-003089). The trial is registered with ClinicalTrials.gov (registration number NCT06122064, registered on 30 October 2023). This protocol is reported following the SPIRIT (Standard Protocol Items: Recommendations for Interventional Trials) guidelines (see Additional file).

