### Allocation: sequence generation {16a}

#### Patient allocation:

Eligible patients will be allocated at 1:1 ratio into either usual care alone or NSCLC Choice. Block randomization will be completed using random block sizes stratified by clinician. The randomization will be carried out by a statistician using the REDCap platform (18, 19)

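### The stated 82% and 80% power, falling as patients per clinician rise, do not fit randomisation within clinician; on the plan's own inputs and a common treatment effect, power is about 85% with 20 or 10 clinicians

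*Protocol article*

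**What the plan says.** Under Sample size estimation {14}, "The targeted sample size is 100 patients", and "SDMQ-9 has an estimated mean value of 70 at baseline, with a standard deviation of 20". The first scenario begins "Assuming an average cluster size of 5 patients per clinician and 20 clinicians" and takes the ICC as 0.01; the claim made for it is that "we would achieve 82% power to detect a 12-point increase in the intervention group (N=50 per group"), for a two-sided test at the 5% level. The second scenario reads: "If 10 clinicians are recruited, with an average cluster size of 10 patients per clinician, we would have 80% power".

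Trial Design {8} says "We will conduct a patient-level randomized controlled trial", with 1:1 assignment. Under Allocation: sequence generation {16a}, "Block randomization will be completed using random block sizes stratified by clinician". The section on usual care encounters adds that the clinician is told each patient's allocation before entering the room. Each clinician is therefore meant to see patients from both arms.

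Statistical methods {20a} and {20c} plan a t-test adjusted for clustering by clinician for the arm comparison. Hierarchical models with clinician random effects are kept for analyses that adjust for anything besides arm.

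**The concern.** The power paragraph treats clinicians as clusters whose size costs power: with N fixed at 100, doubling patients per clinician takes power from 82% to 80%. That is how a trial behaves when whole clinicians are randomised and all of a clinician's patients are in one arm. Here clinician is crossed with arm, so a clinician who scores high or low does so in both arms, and most of that effect drops out of the comparison.

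The practical stake is modest. The paragraph suggests that recruiting 20 clinicians instead of 10 buys power, which its own inputs do not support. The Limitations section also hopes to inform a larger multicentre trial using similar methods, where the same approach could mislead more if the ICC were higher. Finally, if the cluster-adjusted t-test in the statistical methods applies the same inflation, the primary comparison itself would be needlessly conservative.

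**Working it through.** **Inputs, all from Sample size estimation {14}:** difference 12, SD 20, n = 50 per arm, two-sided alpha 0.05, ICC 0.01, m = 5 (20 clinicians) or m = 10 (10 clinicians). Difference and SD are taken to be on the same scale, so only 12/20 = 0.6 matters. Power is from the noncentral t distribution with 98 df unless stated.

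**Step 1: no clustering.** SE = 20·√(2/50) = 4.000; 12/4.000 = 3.000; power 84.4%. This reproduces neither printed figure.

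**Step 2: the plan's figures.** Inflate the variance by DE = 1+(m−1)ICC, so SE = 4.000·√DE.

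| Scenario | DE | SE | 12/SE | Power (t) | Power (normal) | Stated |
|---|---|---|---|---|---|---|
| 20 clinicians, m = 5 | 1.04 | 4.079 | 2.942 | 83.0% | 83.7% | 82% |
| 10 clinicians, m = 10 | 1.09 | 4.176 | 2.873 | 81.2% | 82.0% | 80% |

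The direction matches and the size is close. Cutting the effective n per arm down to whole numbers (50/1.04 → 48; 50/1.09 → 45) gives 82.9% and 80.4%. Allowing for unequal cluster sizes, with DE = 1+((1+CV²)m−1)ICC and an assumed CV of 0.65 that is not in the article, gives 82.2% and 79.7%.

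**Step 3: the design as described.** With equal numbers per arm within each clinician and a common treatment effect, the clinician effect cancels:

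Var(difference) = (2·SD²/n)(1−ICC) = (2·400/50)(0.99) = 15.84, so SE = 3.980 and 12/SE = 3.015.

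Power is 84.7% with 98 df. After losing degrees of freedom for clinicians it is 84.6% (79 df, 20 clinicians) and 84.7% (89 df, 10 clinicians). Cluster size m does not appear in the formula.

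**Step 4: imperfect balance.** Five patients cannot be split evenly, and blocks may be incomplete. A random-intercept model with assumed blocks of 2 or 4 and unequal clusters (assumed CV 0.65) averages 84.6% (20 clinicians) and 84.7% (10). A plain t-test simulated under within-clinician allocation gives 84.2% and 84.5%. With clinician as a fixed effect, power is about 83% (20 clinicians) and 84–85% (10), so it does not fall when clinicians are fewer.

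**Step 5: effect varying by clinician (assumption).** Let the treatment effect have between-clinician variance of 5% of the total, 0.05·400 = 20. The variance of the difference becomes 15.84 + 20/20 = 16.84 or 15.84 + 20/10 = 17.84, giving 82.5% and 80.3% with 98 df. With degrees of freedom equal to clinicians minus one, these are 79.2% and 71.6%. At 1% of the total, the 98-df figures are 84.3% and 83.9%.

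**Step 6: other ICCs (assumed, except 0.01), m = 10, 98 df.**

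| ICC | Power with 1+(m−1)ICC | Power with 1−ICC |
|---|---|---|
| 0.01 | 81.2% | 84.7% |
| 0.05 | 69.4% | 86.2% |
| 0.10 | 57.7% | 87.9% |

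**The case against.** **The formula is not printed.** A reader might infer that the sponsor certainly used 1+(m−1)ICC. The article does not support that certainty: with 98 df the formula gives 83.0% and 81.2%, which do not round to 82% and 80%, and a closer match needs truncated effective sample sizes or an assumed cluster-size variation. Within-clinician randomisation with a 5% treatment-by-clinician variance fits about as well (82.5% and 80.3%). So the source is an inference. But the article states no such variance, only an ICC, and its models name clinician random main effects. The mismatch with the stated design does not depend on knowing the source.

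**Clinician numbers may matter after all.** A reader might infer that power never depends on how many clinicians take part. That goes too far. The section on mode of use lets clinicians vary or withhold the tool, and retraining is clinician-specific, so an effect that differs by clinician is plausible and fewer clinicians would then cost power (Step 5). A test whose degrees of freedom come from the number of clinicians would also lose power even with a common effect: 81.6% with 19 df and 76.5% with 9 df. This stands as a limit on the conclusion. It does not rescue the printed scenarios, which state neither assumption.

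**The planned test may be the inflated one.** If the cluster-adjusted t-test uses the same inflation, 82% and 80% roughly describe that test. The form of the adjustment is not given. This is a reason to change both sections together.

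**Nothing in the trial changes.** Largely true. N is set by resources, the error is conservative, and the abstract's claim of more than 80% power survives. The larger gaps in Step 6 rest on ICCs that are not this trial's.

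**Conclusion.** The power paragraph does not match the stated design. On its own inputs, with patients randomised within clinician and a common treatment effect, power is 84.6–84.7%, or about 85%, for both scenarios. The printed 82% and 80% are too low by 84.6 − 82 = 2.6 and 84.7 − 80 = 4.7 points, and the fall between them does not follow from an ICC of 0.01.

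This rests on three assumptions: roughly balanced allocation within each clinician, an effect that does not vary by clinician, and an analysis with patient-level degrees of freedom that does not inflate the variance by 1+(m−1)ICC. It does not show that the trial is underpowered or that the sample size should change. It is a cheap correction to a figure readers will rely on.

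**What to change.** 1. Under Sample size estimation {14}, replace the two scenarios with wording such as:

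> With 50 patients per arm randomised 1:1 within clinician, an SD of 20, an ICC of 0.01 and a two-sided alpha of 0.05, power to detect a 12-point difference is about 85% (84.6–84.7% with 20 or 10 clinicians), assuming that the treatment effect does not vary by clinician.

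2. Drop the 82% and 80% cluster-size scenarios. If dependence on clinician numbers is to be shown, give it as a sensitivity analysis with the assumed treatment-by-clinician variance and degrees of freedom written out.

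3. Under Statistical methods {20a} and {20c}, state that the primary comparison accounts for clinician as a stratum crossed with arm. The hierarchical model already named, with a clinician random intercept, would serve if it is also used for the arm-only comparison. If the adjusted t-test is kept, say how it adjusts and that it does not multiply the variance by 1+(m−1)ICC.

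The cost is one reworded paragraph and one clarified sentence. The sample size, alpha, target difference and allocation scheme stay as they are.
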